### Circulating factors in serum/plasma

Analytical laboratory measurements including but not limited to factors relevant to iron metabolism (eg. Transferrin), inflammation (eg. IL-6, TNF-a), oxidative stress (eg. TBARs) and metabolic/vascular health will be performed. Samples will be analysed at accredited external laboratories as required under service level agreements between King’s College Hospital and external contracted parties.

### MRI spectroscopy

Forty participants were invited to attend MRI spectroscopy visit at baseline and 4 weeks. Skeletal muscle PCr t1/2 was measured using 31phosphorous magnetic resonance spectroscopy (^31^P-MRS) on a Phillips Achieva MR scanner. This non-invasive technique enables real-time quantification of skeletal muscle energetic molecules (PCr and adenosine triphosphate ATP) during exercise and recovery in-vivo. During exercise, PCr is progressively depleted and then rapidly resynthesized during recovery. Because PCr replenishment is performed exclusively by mitochondria, the rate of PCr recovery after exertion is proportional to mitochondrial function. In addition to the CKD patients, a control population of 8 CKD non-iron deficient subjects and 6 healthy volunteers attended a baseline visit to further validate this technique. The MRI spectroscopy was performed at the King’s College London (KCL) MRI unit located at St Thomas’ Hospital by KCL staff and the research fellow. Where possible, patients having MRI spectroscopy imaging also had muscle biopsies.

### Patient reported outcomes: fatigue, functional impairment, and quality of life questionnaires

Participants were asked to complete the following questionnaires at baseline to capture data about fatigue, functional impairment, and quality of life:The Chalder Fatigue Questionnaire is an 11-item questionnaire measuring the severity of physical and mental fatigue on two separate subscalesThe Work and Social Adjustment Scale is a valid and reliable self-report scale of functional impairment attributable to an identified problem (i.e. fatigue)The Kidney Disease Quality of Life short-form 1.3 questionnaire is a preference-based measure of health (KD QoL-SF-36) questionnaire, a standardized survey used to assess patient health [24].

Questionnaires were repeated at 4 and 12 weeks.

### Safety and monitoring of the intervention

Serious adverse events were identified and documented on the eCRF at routine visits, based on participant reports and primary or secondary care reports. In addition, episodes of infection requiring hospitalisation and other infection episodes and cases of vascular access thrombosis were documented. In addition, haemoglobin, ferritin, platelet levels, and other laboratory measurements detailed above were monitored.

### Other outcomes

#### Qualitative Study – people living with chronic kidney disease

Individual semi-structured interviews were conducted to understand the impact of CKD on the lived experience, expectations of the iron and exercise interventions before the trial, and their experiences afterwards. A sample of 20 participants were interviewed at entry to and exit from the study. Participants were selected using purposive sampling to ensure varied experiences and viewpoints are represented, for example, including people in both study arms, and including people with different participation rates and response to the intervention. Interviews were conducted face-to-face or via telephone, according to participant preference, and lasted approximately one hour. Face-to-face interviews were conducted in a private room, on a separate visit or combined with the baseline visit depending on participant preference. The interviews were digitally recorded and transcribed verbatim by a professional transcription service. Thematic analysis (Braun and Clarke, 2006) was used to interpret the data and identify themes. The data was stored and managed in QSR NVivo software.

### Sample size

#### Primary outcome: 6MWT distance

The choice of endpoint measures to be studied were chosen to provide clinical relevance. Studies that have evaluated the clinically meaningful change in the distance walked on the 6MWT in patients with heart failure [25, 26] indicate that a clinically meaningful improvement in 6MWT distance is between 32 and 45 m. Calculations from the FAIR-HF study [27] and a study in patients with CKD [28] suggested a clinically meaningful improvement in 6MWD of up to 40 m. We have therefore taken this to be the mean clinically important difference (MCID) at the 4-week primary outcome endpoint. An estimated sample size to detect a clinically meaningful difference of 40 m with a SD of 56 m (derived from the higher SD reported by Tang et al. [28]) at 80% power and 5% alpha revealed a requirement of 62 participants. We aimed to recruit at least 70 patients to enable dropouts and ensure that 4-week primary outcome data were collected for at least 62 patients.

### Other outcomes

(i) MRI spectroscopy: Using unpublished data from the FERRIC-HF II ([name]) trial assessing the impact of iron repletion on skeletal muscle phosphocreatine recovery in anaemic and non-anaemic heart failure patients, mean (± SD) phosphocreatine recovery halftime at study end was 33 ± 7 s in the non-anaemic cohort. To detect a difference of 7 s at 80% power and 5% alpha, we needed at least 32 patients in total. We planned to recruit 40 patients from the total sample to undergo MRI spectroscopy analyses to enable drop-out and insufficient imaging quality.

ii) Muscle biopsy: We also estimated that 40 patients from the total sample would be needed to undergo a muscle biopsy procedure at baseline and four weeks, to enable 16 participants in each arm to detect differences in proposed analyses allowing for drop-out and insufficient sampling. The team has previously performed three exercise intervention studies [29, 30] with sample sizes in each arm ranging from 11 to 18 participants. In all these studies, the team were able to detect significant differences following exercise at the molecular level.

iii) Muscle biopsy phosphocreatine recovery: Using unpublished data from the FERRIC-HF II ([name]) trial assessing the impact of iron repletion on the rate of muscle oxygen consumption in heart failure patients, mean (± SD) ex-vivo muscle oxygen consumption at study end was 0.58 ± 0.22 micromol/min/mg. To detect a meaningful difference of 0.25 micromol/min/mg skeletal muscle phosphocreatine recovery at 80% power and 5% alpha, at least 26 participants are needed, thus we aimed to recruit at least 36 patients to allow for dropouts and patients with poor quality muscle biopsies.

### Statistical analysis plan

#### Descriptive analyses

The results will be constructed according to CONSORT. To assess the comparability of randomised groups at baseline, descriptive summaries of clinical and socio-demographic variables will be presented for each study group. Means and SD will be presented for quantitative variables, and numbers and proportions for categorical variables. No significance tests will be undertaken. If any quantitative variables are highly skewed, medians and interquartile ranges will also be presented.

Descriptive summaries will similarly be provided for each outcome variable, at both 4 weeks and 12 weeks, by study group. The proportions of participants with missing data for each outcome variable will be presented by study group. Baseline characteristics of those with missing follow-up data for key outcomes will be compared descriptively to those with complete data.

Adverse events and serious adverse events (SAE), including serious adverse reactions (SAR) and suspected unexpected serious adverse reactions (SUSAR) will be tabulated. The reasons for any withdrawals from the trial will be summarised.

### Analysis of primary outcome

The difference in means for distance walked during 6MWT (metres) at 4 weeks (primary outcome) between patients randomised to IV iron and placebo will be analysed using an ANCOVA model, using baseline 6MWT distance and the binary stratification variable ferritin (defined as whether or not baseline ferritin is over 50 µg/L) as covariates [31]. Data will be analysed under intention-to-treat assumptions. The mean difference and associated confidence interval will be reported. All analysis will be undertaken in Stata version 15, or a later version if available.

### Analysis of secondary outcomes

The ANCOVA described above for the primary outcome will also be performed for the 6MWT distance (metres) at 12 weeks, and for the other secondary endpoints described earlier. In each case, the baseline value of the variables and the binary stratification factor will be used as covariates.

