### Secondary objectives

The secondary objectives were: i) to assess the effect of intravenous iron compared to placebo on physical capacity, quality-of-life, and skeletal muscle metabolism at 4 weeks; and ii) to assess the effect of intravenous iron compared to placebo on physical capacity, quality-of-life, and skeletal muscle metabolism at 12 weeks following an 8-week exercise programme offered to all trial patients.

Specifically, we propose to examine whether a routine strategy of IV iron therapy in patients with stages 3–4 CKD who are iron-deficient leads to improvements in exercise capacity and the following outcomes.

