### Interventions

Participants were randomised to receive either ferric carboxymaltose (Ferinject®) or placebo at the baseline visit. All participants were offered eight weeks of exercise training between week 4 and week 12 assessment visits. Participants allocated to the placebo group were followed up in routine clinic after completing the trial and offered standard treatment, including treatment for their iron deficiency if still present.

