### Assessment outcomes and their measurement

#### Baseline clinical information and study visits

Following screening, willing, and eligible participants were invited to attend a baseline visit, at which baseline investigations were performed (Table 2**)**. The baseline/randomisation visit(s) occurred no more than four weeks after the patient had successfully passed a screening visit. The assessments were split over two visits if the participant preferred. Demographic data (date of birth, sex, ethnicity, smoking status, alcohol intake, body mass index (BMI), and primary aetiology of CKD were collected and recorded. A detailed disease history including cardiovascular co-morbidity and list of concomitant medications was taken. Vital signs were recorded including blood pressure. A physical examination was not required.

**Table 2 Tab2:** Overview of trial schedule

**Procedure**	**Screen Visit**	**Baseline** **Visit 1** **(Local site)**	**Baseline Visit 2** **(KCH)**	**Week 4** Visit 1 (Local)	**Week 4 Visit 2 (KCH)**	**Week 12** **Visit 1 (Local)**
		Within 4 weeks of Screening visit		4 weeks ± 4 days from IMP Administration		12 weeks ± 14 days from IMP Administration
Patient information and informed consent	X					
Inclusion / Exclusion criteria	X					
Demographic data and medical history	X					
Concomitant medications	X	X	X	X	X	X
Vital Signs	X	X	X	X	X	X
Weight	X					
Height, weight, BMI, waist-to-hip ratio		X		X		X
IMP administration			X			
Exercise prescription				X		
Full blood count	X			X		X
Ferritin & TSAT	X			X		X
U + E, Creatinine, LFTs, CRP	X			X		X
eGFR, Phosphate	X			X		X
Soluble Transferrin Receptor and stored sera/plasma/whole blood (EDTA)			X		X	X
Exercise capacity (6MWD, VO_2_ peak)		X		X		X
Muscle strength (isokinetic dynamometry)		X		X		X
Fatigue Severity Score (Chalder Fatigue Questionnaire)		X		X		X
Functional impairment (WSAS Questionnaire)		X		X		X
Quality of life (KDQOL-36)		X		X		X
Functional capacity (STS60)		X		X		X
MRI spectroscopy (subset of participants)			X		X	
**Procedure**	**Screen Visit**	**Baseline** **Visit 1** **(Local site)**	**Baseline Visit 2 (KCH)**	**Week 4** **Visit 1 (Local)**	**Week 4 Visit 2 (KCH)**	**Week 12** **Visit 1 (Local)**
		Within 4 weeks of Screening visit		4 weeks ± 4 days of IMP Administration		12 weeks ± 14 days of Baseline visit
Muscle metabolism via muscle biopsy (subset of participants)			X		X	
Qualitative Interview		X			X (if no exercise)	X
Adverse Events		X		X		X

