### Six minute walk test

The primary endpoint for this study was the change in 6MWT distance between baseline and 4 weeks. The outcome was also performed at 12 weeks following the 8-week exercise training programme. Distance (in metres) was measured during a self-paced, standardised 6MWT conducted around a level, 30.5 m circuit [22]. The walk test was completed twice following sufficient rest (20 min) to allow heart rate to return to resting. The results from the second test were used for analysis.

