#### Missing outcome data

If there are missing data for the primary outcome of 6MWT at 4 weeks, several strategies will be considered. If missingness is below 5%, and missingness is not thought to be isolated to a particular clinically relevant subgroup, then a complete-case analysis (CCA) will be performed [35]. If there is more than 5% missing data, then alternative approaches will be used.

If participants with missing 4-week 6MWT data have post-randomisation variables predictive of missingness of 4-week 6MWT (e.g., 12-week 6MWT) *and* predictive of the 4-week 6MWT values themselves, then a linear-mixed model (LMM) will be performed. This will assume that the missing data is missing at random (MAR) conditional on these post-randomisation variables. Unlike CCA, a LMM can include potentially informative post-randomisation variables without impacting the treatment effect estimates. LMMs also perform similarly to multiple imputation (MI) in such a multivariate scenario (SAP15), whilst not requiring completeness of the post-randomisation auxiliary variables. Although it is unlikely that most participants with missing 4-week 6MWT will have 12-week 6MWT data, there may be other post-randomisation variables associated with 4-week 6MWT and its missingness.

If such post-randomisation variables are not present, patterns of missingness in *baseline* variables will be assessed. If the data is thought to be MAR conditional on observed baseline variables, then a complete-case analysis (CCA) adjusted for variables predictive of missingness will be performed. Under the MAR assumption, this gives unbiased and efficient treatment effect estimates, and generally performs better than alternative methods like MI [34].

If there is evidence of an interaction being predictive of both the outcome and missingness of the outcome (e.g., see “Method for handling the impact of COVID-19” section below), then MI will be used instead of the LMM and adjusted-CCA approaches outlined above. MI has the flexibility to handle both the interaction term and the other variables predictive of missingness and gives an unbiased estimate of the average treatment effect (ATE) in the analysis model [34].

The impact of the MAR assumption in all the above approaches will be assessed via a sensitivity analysis, in which a range of plausible values for the missing outcome data will be assumed, and corresponding treatment effect ranges reported.

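### The 12-week ANCOVA drops patients seen at week 4 but not at week 12 and ignores their week 4 data, which can pull a real iron effect toward zero

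*Protocol article*

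**What the plan says.** Secondary objective (ii) compares iron with placebo "at 12 weeks following an 8-week exercise programme offered to all trial patients". Training is optional (Interventions: "All participants were offered eight weeks of exercise training between week 4 and week 12 assessment visits"), and the 12-week walk test is placed after it (Six minute walk test: "The outcome was also performed at 12 weeks following the 8-week exercise training programme").

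Under Analysis of secondary outcomes, "The ANCOVA described above for the primary outcome will also be performed for the 6MWT distance (metres) at 12 weeks", and likewise for the other secondary endpoints. The covariates are fixed: "In each case, the baseline value of the variables and the binary stratification factor will be used as covariates".

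The section Missing outcome data opens: "If there are missing data for the primary outcome of 6MWT at 4 weeks, several strategies will be considered". It then sets out a linear mixed model, an adjusted complete-case analysis, multiple imputation and a sensitivity analysis for the missing-at-random (MAR) assumption, all for that 4-week outcome. Only the rules in the COVID-19 section, on site closure, infection and before/after-break status, extend to the 12-week walk and other outcomes. The non-compliance section considers the infusion and not the training.

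**The concern.** An ANCOVA on the 12-week value can use only patients who have that value. Outside the COVID-19 rules, nothing stated brings back those who do not. Between weeks 4 and 12 patients are offered three one-hour sessions a week for eight weeks, so this is the interval in which losing contact is most likely. Whether a patient stays may depend on how he or she walks and feels at week 4, which is what iron is meant to change. If so, the patients left at week 12 are selected differently in the two arms, and the comparison is no longer that of the randomised groups.

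The plan also uses its repeated measurements in the less helpful direction. It lets the 12-week walk inform a missing 4-week value, while conceding that most patients missing week 4 are unlikely to have week 12. The reverse pattern, week 4 observed and week 12 missing, has no such provision.

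**Working it through.** **The plan's own figure.** Sample size section: difference 40 m, SD 56 m, 80% power, 5% alpha (two-sided assumed). Per arm: 2 × (1.960 + 0.842)² × 56² / 40² = 30.8, rounded up to 31, so 62 in total. This reproduces the stated 62. The recruitment target allows (70 − 62)/70 = 11.4% loss by week 4. No week 12 retention figure is given.

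**Where the bias comes from.** Let e4 and e12 be the week 4 and week 12 residuals after baseline adjustment, in SD units, with correlation ρ. If attendance at week 12 depends on the week 4 result, then

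bias = ρ × 56 m × (mean e4 among iron attenders − mean e4 among placebo attenders).

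In all randomised patients the bracket is zero. If poor walkers at week 4 tend to be absent and iron raises the week 4 walk, the placebo arm loses more of its poor walkers. The bracket is then negative.

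**Inputs.** From the article: 75 randomised 1:1 (37 and 38), effect 40 m, SD 56 m, baseline SD 174 m. Assumed: the effect is 40 m at both visits, 56 m is the residual SD at both visits, ρ is 0.6 or 0.8, and 15%, 30% or 40% are absent at week 12. Log-odds of attendance rise by 0, 0.7 or 1.5 per residual SD of the week 4 result. In odds these are factors of 1, e^0.7 = 2.0 and e^1.5 = 4.5 per 56 m.

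**Comparison.** (a) ANCOVA of week 12 on arm and baseline in attenders. (b) The maximum-likelihood repeated-measures estimate: week 4 on arm and baseline in everyone, week 12 on arm, baseline and week 4 in attenders, then combined. 4,000 simulated trials per scenario, true effect 40 m.

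| Dependence on week 4 | ANCOVA, range of means | Repeated measures |
|---|---|---|
| 0.7 per SD (moderate) | 37.0 to 38.6 m | 39.7 to 40.2 m |
| 1.5 per SD (strong) | 31.7 to 36.5 m | 39.7 to 40.2 m |

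Strong dependence with ρ = 0.8, mean (SE):

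| Absent at week 12 | ANCOVA | Repeated measures |
|---|---|---|
| 15% | 35.1 (13.6) | 39.9 (13.7) |
| 30% | 32.6 (14.6) | 40.0 (14.1) |
| 40% | 31.7 (15.6) | 40.2 (14.7) |

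The moderate loss is 40 − 38.6 = 1.4 m to 40 − 37.0 = 3.0 m. The largest is 40 − 31.7 = 8.3 m, or 8.3/40 = 21% of the effect and 8.3/15.6 = 0.53 of a standard error. By the formula, 8.3/(0.8 × 56) = 0.19, so the bracket is about −0.19 SD.

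**No dependence.** Both methods are unbiased and only the SE differs. At 30% absent it is 14.2 to 14.5 m (repeated measures) against 15.5 to 15.9 m (ANCOVA). At 40% absent it is 14.8 to 15.7 m against 17.1 to 17.3 m.

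**Second check.** 400,000 patients per scenario, log-odds 1.0 per SD, ρ = 0.6, 10% to 40% absent:

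- Equal dependence in both arms, 40 m effect: bias −1.6 to −3.6 m.
- Equal dependence, no iron effect: about 0.
- Absence depends on baseline only: about 0.
- Dependence in the placebo arm only: −3.7 to −12.4 m, and present even with no iron effect (−3.7 to −11.1 m).

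Using the week 4 value brought the bias to within 0.3 m of zero in every case.

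**The case against.** **Who is measured and analysed at week 12.** A reader might infer that non-exercisers have no 12-week handling at all. The article does not support that. Follow-up visits and Table 2 schedule the week 12 measures for all patients, timed from treatment or baseline and never from training. Objective (ii) refers to a programme that is offered, and the ANCOVA comes from a section that states intention to treat. A non-exerciser who attends is analysed as observed.

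**An exit at week 4.** A reader might also infer that patients who do not train leave the trial at week 4. Table 2 has the entry "X (if no exercise" at Week 4 Visit 2, and the qualitative section says "A sample of 20 participants were interviewed at entry to and exit from the study". But the entry sits only in the interview row, for that sample of 20. An earlier closing interview for someone with no training to describe does not cancel the week 12 assessments. Not exercising and not attending are different events, and nothing in the article links them.

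**Existing cover.** The descriptive analyses report missing data for each outcome by group, compare baseline characteristics of patients with and without key outcomes, and summarise reasons for withdrawal. The COVID-19 rules give an adjusted complete-case analysis or imputation where break status predicts missingness. This makes a problem visible, but does not bring the week 4 value into the 12-week estimate.

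**The full SAP may cover it.** It may, and silence alone would be no finding. Here, however, the article fixes the 12-week model and its covariates, and words its missing-data strategy for the 4-week walk.

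**Size.** The 8 m figure needs 40% absent, ρ = 0.8 and a 4.5-fold change in odds per 56 m, which implies about 49% absent on placebo against 31% on iron in a blinded trial. That is an extreme case. Dependence in one arm only is harder still to expect under blinding. With equal dependence and no iron effect there is no bias, so this mechanism dilutes a real effect and does not create a false one.

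**Conclusion.** The point stands as a moderate weakness in the secondary analyses. As written, the 12-week model discards patients who have a week 4 but no week 12 value, together with their week 4 information. The resulting bias is conditional: it needs absence to depend on the week 4 response and, with equal dependence in both arms, a real iron effect. Under those conditions the 12-week estimate falls short by about 1 to 3 m of 40 m with moderate dependence and by up to about 8 m at the strong end, within an SE of about 14 to 17 m. If absence is unrelated to week 4, the cost is precision only, for example an SE of 17.3 m instead of 14.8 m at 40% absent and ρ = 0.8. Attrition, correlation and dependence are all assumed, so the article cannot show that a bias will occur. The 4-week primary outcome precedes training and is untouched.

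**What to change.** For each outcome measured at both follow-up visits, estimate the 12-week arm contrast from one repeated-measures linear model. Include arm, visit, arm-by-visit, baseline-by-visit and ferritin stratum, with unstructured covariance across weeks 4 and 12. Include every randomised patient with either follow-up value.

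The smaller alternative is to keep the ANCOVA and state that the mixed-model strategy and the MAR sensitivity analysis in Missing outcome data also apply at week 12, with the week 4 value as the informative post-randomisation variable.

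One sentence should also confirm that week 12 outcomes are analysed whatever the training uptake, and that the Table 2 entry concerns the interview only, if that is what is meant.

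The cost is wording and one standard Stata model per repeated outcome, with no extra visits or patients, and the plan already accepts mixed models for week 4. The small downside is a few more parameters and reliance on missing at random given week 4. That is a weaker assumption than the completer ANCOVA makes.
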